## Abstract

**Background:**

Cognitive Stimulation Therapy (CST) is a psychosocial evidence-based group intervention for people with dementia recommended by the UK NICE guidelines. In clinical trials, CST has been shown to improve cognition and quality of life, but little is known about the best way of ensuring implementation of CST in practice settings. A recent pilot study found that a third of people who attend CST training go on to run CST in practice, but staff identified a lack of support as a key reason for the lack of implementation.

**Methods/design:**

There are three projects in this study: The first is a pragmatic multi-centre, randomised controlled trial (RCT) of staff training, comparing CST training and outreach support with CST training only; the second, the monitoring and outreach trial, is a phase IV trial that evaluates implementation of CST in practice by staff members who have previously had the CST manual or attended training. Centres will be randomised to receive outreach support. The primary outcome measure for both of these trials is the number of CST sessions run for people with dementia. Secondary outcomes include the number of attenders at sessions, job satisfaction, dementia knowledge and attitudes, competency, barriers to change, approach to learning and a controllability of beliefs and the level of adherence. Focus groups will assess staff members’ perceptions of running CST groups and receiving outreach support. The third study involves monitoring centres running groups in their usual practice and looking at basic outcomes of cognition and quality of life for the person with dementia.

**Discussion:**

These studies assess the effects of outreach support on putting CST into practice and running groups effectively in a variety of care settings with people with dementia; evaluate the effectiveness of CST in standard clinical practice; and identify key factors promoting or impeding the successful running of groups.

**Trial registration:**

Clinical trial ISRCTN28793457.

## Background

The worldwide population is rapidly aging [1], resulting in increased numbers of people with dementia [2]. The increase in demand for dementia-related services has long been anticipated. However, the planning and provision of services for people with dementia appear to be failing to meet increasing requirements [3]. Two thirds of people living in care homes have dementia, which in turn leads to an increasing level of dependency that can be attributed to a lack of stimulation, increased behavioural problems and the use of anti-psychotic medication [4]. There is a need to provide services in the community but also to improve the availability of psychosocial interventions.

CST is an evidence-based group programme for people with mild to moderate dementia [5]. A review of reality orientation (RO) [6] helped to develop CST as a brief psychosocial group intervention, focussing on implicit information processing. The development of CST has followed the Medical Research Council (MRC) guidelines for the development and evaluation of complex interventions [7]. Cognitive stimulation leads to benefits in cognition and quality of life in the person with dementia [8], is shown to be cost effective and compares favourably with cholinesterase inhibitors for Alzheimer’s disease [5,9]. Currently cognitive stimulation is the only non-pharmacological intervention to improve cognition recommended in the NICE-SCIE Guidelines for Dementia [10], which recommend that all people with mild to moderate dementia should be ‘given the opportunity to participate in a structured group cognitive stimulation programme’.

CST is a twice-weekly, 7-week programme of stimulating 45-min group activities for people with dementia. A pilot study [11] of CST with an additional 16 weeks of once-weekly maintenance CST (MCST) sessions found a continued improvement in cognitive function for the people with dementia receiving maintenance CST. A large-scale RCT of maintenance CST (24 weeks of once-weekly sessions) versus CST only [12] has recently been completed as part of the SHIELD (Support at Home Interventions to Enhance Life in Dementia) project. The programme includes 7 weeks of CST and a further 24 weeks of maintenance CST sessions.

In recent years there has been an increase in the provision of CST, with around a third of the community mental health teams in the UK reporting using it [13]. This has been facilitated by the publication of the CST ‘Making a difference’ manual and the maintenance CST manual ‘Making a difference 2’ with a CST staff-training DVD [14,15]. However, there has been little research on the long-term implementation and evaluation of CST in practice.

A recent study found that after attending a CST training course, one third of the staff went on to implement CST groups in practice [16]. All staff members felt skilled enough to run the groups; however, they identified the need for management support, regular supervision, supervision from a specialist, online forums and additional training as useful in starting and running groups. Previous research into CST has reached phase III of the MRC framework for complex interventions [7]. This research aims to study the long-term implementation of CST within two linked trials and conduct a phase IV trial that will evaluate the effects of training, and the effects of outreach support and the long-term effects of CST in practice, and will help to understand the barriers and facilitators related to implementing CST in practice.

## Methods

### Design

This study includes three projects. The training and outreach trial and the monitoring and outreach trial differ in how staff members are recruited and in their previous exposure to training in CST. The observational study focuses on the effects of CST on people with dementia in the practice context. The three projects together will provide evidence on the most effective way of facilitating the implementation, uptake and effectiveness of the approach in a clinical context (see Table 1).

**Table 1 T1:** Project overview

**Title**	**Training and outreach trial**	**Monitoring and outreach trial**	**Observational study**
**Aim**	To assess the effectiveness of staff training and outreach support	To assess the implementation in practice of CST and outreach support	To assess the effectiveness of CST in practice
**Participants**	Dementia care staff	Dementia care staff	People with dementia
	No previous CST experience or training	Previously received CST manual/training	
**Number**	120	120	100
**Resources**	CST manual maintenance CST manual DVD	CST manual maintenance CST manual DVD	CST manual maintenance CST manual DVD
**Training**	Yes	Variable	Variable
**Outreach**	50%	50%	No
**Assessment timeframe**	Baseline, 6 and 12 months	Baseline, 6 and 12 months	Before and after CST (0, 7 or 0, 14 weeks) and maintenance CST (31 or 38 weeks)

### Training and outreach trial (TROU)

The design is a pragmatic, multi-centre, single-blind, two treatment arm, randomised controlled trial. All participants receive the training package as treatment as usual (TAU) consisting of the 1-day CST training, training DVD, CST manual and maintenance CST manual. Participants in the intervention group also receive outreach support (local coordinator, email support and online forum). The sample is dementia care staff from specialist and non-specialist dementia care settings. The staff are cluster randomised according to place of work, before the training day, to receive outreach support or not. Each staff member completes three questionnaires, the first before the training day and at 6 and 12 months thereafter (Figure 1).

**Figure 1 F1:**
[figure not shown]
Flow diagram of training and outreach trial and assessment schedule.

### Recruitment

Recruitment to the trial includes staff from care homes, day centres and NHS Trusts from various locations across the UK. The trial is advertised through the Journal of Dementia Care, and the National Care forum and referrals are made through the commercial CST training day. The research team is then able to assess their eligibility for participating in the research. Follow-ups will also be made with centres that have expressed a previous interest in CST or attending a CST training day.

### Participants

Staff members are screened to ensure they meet the inclusion criteria: (1) adequate written and spoken English, (2) able to complete online assessments at three different time points, (3) have at least two other team members with whom to run groups, (4) agreement from their management to have 2 h set aside per week to run the CST groups and 1 h following on from this for the 24-week maintenance CST programme, and (5) are able to provide between five to eight people with mild to moderate dementia who are willing to participate and meet the inclusion criteria (described in the observational arm). A minimum of three staff members is recruited per centre for logistical reasons of being able to consistently run the groups. Up to 40 centres are needed to be able to recruit the 120 staff members required for the trial. Working on the premise of a 15% attrition rate, the sample size will provide sufficient numbers for the staff training outreach support/no outreach support to estimate effect size and the feasibility of the trial. The attrition rate is an estimation based on previous research conducted in CST [12].

### Training package

The CST and maintenance CST manual along with the DVD are distributed to all staff members participating in the trial. The CST ‘Making a difference’ manual describes an evidence-based programme of group activities providing stimulation for people with mild to moderate dementia based on the principles of person-centred care. The maintenance CST manual, ‘Making a difference 2’, follows on from the original programme and includes a 24-week structured programme of activities aimed at challenging yet empowering the person with dementia and comes with a staff-training DVD. The staff-training DVD comprises an introduction by [name] as to what CST is, a table listing the order of the CST and maintenance CST sessions. and key principles. In addition to this, there is video footage of CST sessions with people with dementia for staff to observe and discuss. After each clip there are questions based on the key principles to encourage reflective learning and discussion. All staff members attend a CST training day. The training comprises the different perspectives of dementia, the main psychosocial approaches for dementia, the development and evaluation of CST, the session themes and examples of activities for sessions, key principles, planning of sessions and the setting up of a group, and reflective learning of issues that arise when implementing and running groups. The training uses learning methods such as role-play, small group exercise and use of the training DVD, and time is spent reflecting on the sessions and critically appraising how the session is run. Following on from the training day, it is advised that each session be run with two facilitators to enable them to jointly plan and reflect on the session, and complete the attendance and adherence forms together.

### Randomisation

Cluster randomisation occurs prior to the staff attending the CST training day to ensure that staff members from the same centre receive the same level of support. The allocation ratio for randomisation is 1:1, into either the intervention or TAU. Randomisation is managed by email to the North Wales Organization for Randomized Trials in Health (NWORTH), which is an accredited trials unit, specialising in pragmatic trials.

### Treatment as usual

Staff members within centres that are randomized to the control group deliver the CST as usual but without the additional outreach support. This can vary between centres and has the variability to change over time, but the training package offered to the intervention group will also be available to those in the control group. Therefore, the trial examines the additional effects of the outreach support.

### Intervention

A pilot study conducted by our team identified that outreach support should consist of (1) an online forum, (2) email support and (3) local supervision [16]. The online forum is an online discussion site. It is accessible by user name and password. The first time a person attempts to enter the site, an email is sent to a member of the research team for approval in order to ensure they have been randomised to the intervention group. The use of a login allows us to record the number of people accessing the service, and how many times. Staff members are able to write up a variety of messages ranging from comments on sessions, to questions and advice. A researcher, who has extensive experience of CST and experience of running groups, delivers the email support ([name]) and the service is made available as much as is needed by the staff members. A person familiar with CST and experience in running groups delivers the local supervision. The centre identifies the relevant person; however, if this is not possible a member of the research team provides the support. The role of the local supervisor is to help with the setting up of the CST group and also the practical issues that the staff members encounter when attempting to run CST groups. The supervisor records all the support given.

### Primary outcome measure

The primary outcome measure is number of CST and maintenance CST sessions run in the centre by the follow-up at 31 weeks. This is recorded using the monitoring progress form located in the ‘Making a difference’ manual [14], which includes who was in attendance, level of interest, communication, enjoyment and mood, on a rating scale 1–5. This measure is being completed at the end of each session from baseline to 31 weeks (inclusive of maintenance CST), until the maintenance CST groups have been completed or until the groups have been discontinued.

### Secondary outcome measures

a) The level of adherence to the CST and maintenance CST programme is measured by a adherence list designed as part of the research. It is based on the 18 key principles as developed as part of the maintenance CST programme [15]. The responses are reviewed by a researcher to mark whether staff are adhering to the key principles as laid out in the ‘Making a difference 2’ manual. Any ambiguity of responses given by the participants will be discussed with another researcher until a consensus is reached as to whether they are adhering to the key principles.

b) Job satisfaction [17] is measured using the Minnesota Satisfaction Questionnaire (MSQ). It is made up of 100 questions and comprises 20 dimensions with five items per scale with a 5-point Likert rating scale. The measure has adequate internal reliability.

c) Staff members’ approach to dementia is measured using the Approaches to Dementia Questionnaire (ADQ) [18]. The ADQ has 19 statements about the person with dementia and the care they receive. The scale has high validity and good reliability using Cronbach’s *α* for its person-centeredness and hopefulness subscales [18].

d) Knowledge is measured using the Dementia Knowledge–20 (DK-20) [19]. There are 20 questions for which there are five possible answers. The scale has sufficient reliability and is administered at baseline and final follow-up only.

e) Perceived sense of competence is measured using the Sense of Competence in Dementia care–Staff questionnaire (SCIDS) [20]. It comprises 17 items categorised into four subscales: professionalism, building relationships, care challenges and sustaining personhood. The scale has good internal consistency.

f) Learning characteristics of staff are measured using the brief Learning Transfer System Inventory (LTSI) [16,21]. The constructs of the LTSI are validated using common factor analysis [22,23]. The brief form comprises of 16 questions that are categorized into four major groups: trainee characteristics, motivation, work environment and ability [22]. All the items use five-point Likert-type scales from 1, strongly disagree, to 5, strongly agree.

g) Barriers to change within the workplace are measured using the Barriers to Change Questionnaire (BARCQ) [24]. It comprises 19 questions focussing on: institutional constraints, support from colleagues, philosophical opposition, client dissatisfaction, interference and positive factors. It also allows the addition of any further comments.

h) The emotional and behavioural responses relating to challenging behaviour presented by the person with dementia are measured by the Controllability Beliefs Scale [25]. The scale has 15 items based on a 5-point scale. The height of the score establishes the belief of the staff member in relation to the level of control demonstrated by the person with dementia. The scale has good internal reliability.

i) Focus groups with staff and managers will be conducted in both the TROU and MONOU trial to obtain qualitative data with regards to people’s perception of running groups and outreach support. They will run in a variety of care settings, and follow a semi-structured interview schedule, using inductive thematic analysis to code and analyse the gathered data.

### Consent

Staff members give informed consent and it is made clear that they will be of no disadvantage if they choose not to participate further at any stage during the trial. Consent is also sought from a member of management in order to give staff the optimum chance of carrying out CST in their workplace. Ethical approval was granted June 2011 by East London REC 3.

### Blinding

Although staff members cannot be blinded to their allocation, all assessment data are completed online and independently of the research team. Once the staff member has completed the survey, an administrator on the SHIELD programme team assigns all staff members a code for identification purposes to maintain anonymity throughout the trial. The researcher administering the outreach support has the contact details of the staff members but is unaware of their individual code; hence they are blind in identifying the staff members. However, it is common for participants to inadvertently inform researchers of the strand of the trial they have been allocated to. To reduce the risk of this, once staff members are aware of their code it is emphasised that it is not to be discussed with any members of the research team. This reminder is included in the email sent by a member of the research team to complete the follow-up assessments.

### Monitoring and outreach trial (MONOU)

The design is a pragmatic, multi-centre, single-blind phase IV trial. Participants are staff members from centres that have previously purchased the CST ‘Making a difference’ manual or attended a CST training course. The staff members are currently in possession of the CST manual or attended CST training. In addition to this, they all receive the maintenance CST manual and DVD. It is recorded whether participants have the manual only or manual and training. Centres are cluster randomised into outreach support or no outreach support (Figure 2). The time points for completing the questionnaire are the same as the training and outreach trial. However, they also complete a retrospective questionnaire on their use of CST in practice prior to the research.

**Figure 2 F2:**
[figure not shown]
Flow diagram of the monitoring and outreach trial and assessment schedule.

### Recruitment

Recruitment of staff members who have purchased the manual is based on referrals by Hawker publications. A database of attendees generated from previously run CST training days allows us to approach people who have attended CST training. Staff members are then contacted to determine if they are interested in participating in the study. A CST poster advertises the research on the CST website (http://www.cstdementia.com), SHIELD (http://www.ucl.ac.uk/shield), and through the Journal of Dementia Care. The project is also a UKCRN portfolio-adopted study allowing NHS Trusts nationwide to be able to approach the research team in order to assess their eligibility for participating in the research.

### Participants

Participants are dementia care staff who have the CST manual or attended the CST training day, and are able to implement the CST programme once or twice weekly. The screening and inclusion criteria match those for the training and outreach study but a minimum of one staff member can be recruited per centre.

### Randomisation

Randomisation is identical to the TROU trial. Before randomisation it is recorded who has the manual or manual and training. At various time points during the recruitment of the participants the centres are divided into two clusters, taking into considerations the size of the centre and type of previous training (manual vs. manual and training). This matched pair of clusters is then independently cluster randomized to receive the intervention or TAU by remote email service to N-WORTH. Because of differing numbers per centre we will endeavour to keep similar numbers in the control and experimental group, with an allocation ratio for randomisation of 1:1, into either the intervention or TAU group.

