### Primary outcome measure

The primary outcome is identical to the TROU trial. However, due to the nature of the recruitment, in that people are being recruited who have previously purchased the ‘Making a difference’ manual or attended CST training, it will be dependent on people’s interest in taking part in the research. As a minimum of one staff member can participate per centre; between 40 and 120 centres are required to recruit 120 staff members. This figure also accounts for a 15% attrition rate.

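### Read literally, MONOU makes one random allocation per batch of centres, so its randomised unit is a group of centres and not the centre named elsewhere in the protocol

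*Protocol article*

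**What the plan says.** The protocol article describes MONOU's unit of randomisation in three places.

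- The MONOU design section: "Centres are cluster randomised into outreach support or no outreach support".
- The opening of MONOU's Randomisation section: "Randomisation is identical to the TROU trial". The TROU design section gives that trial's unit: "The staff are cluster randomised according to place of work, before the training day, to receive outreach support or not". TROU's own Randomisation section adds the 1:1 ratio and the email service, and describes no grouping of centres.
- Further on, MONOU's Randomisation section adds a step that is repeated, at unspecified moments, while recruitment is under way: "the centres are divided into two clusters, taking into considerations the size of the centre and type of previous training". Prior training here means having the manual only, or having both manual and training. The step that follows is this one: "This matched pair of clusters is then independently cluster randomized to receive the intervention or TAU by remote email service to N-WORTH". The section closes by aiming for similar numbers in the two arms, "with an allocation ratio for randomisation of 1:1, into either the intervention or TAU group".

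MONOU's Primary outcome measure section gives the expected size: "between 40 and 120 centres are required to recruit 120 staff members". The Analyses section plans a combined TROU and MONOU comparison of mean sessions per centre. The number of batches is not stated, nor is who divides the centres or by what rule.

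**The concern.** In the detailed description, the word cluster means a set of centres, and what goes to the trials unit is one matched pair of such sets. Every centre in a set then receives the same allocation, and chance acts once per batch. Everywhere else the cluster is the centre. A reader cannot tell which unit was randomised, although the primary outcome is counted per centre.

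The division takes account of two factors, centre size and prior training. Whatever else differs between the two halves of a batch, such as setting, region or management support, goes wholly to one arm by a single random decision. With centre-by-centre allocation, such differences would be spread over many decisions. At stake are the number of independent random allocations behind the MONOU comparison, and whether a centre-level analysis that ignores batch keeps its nominal error rate.

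**Working it through.** **Inputs from the protocol.** MONOU centres: 40 to 120. Ratio 1:1. TROU: up to 40 centres (TROU Participants section). Planning values: means 16 and 12, SD 10, alpha 0.05, power 0.8, 200 participants (Analyses).

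**Inputs assumed.** Number of batches k (not stated). Any outcome variance shared by centres in the same half of a batch (not stated).

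**1. The plan's own figure.** Per arm, n = 2(1.96 + 0.84)² × SD²/δ² = 2 × 7.849 × 100/16 = 98.1, so 99 per arm and 198 in total. The stated 200 is reproduced. It counts staff participants and contains no term for batch. It does not use the number of centres, so it neither supports nor contradicts either reading of the randomised unit.

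**2. Randomised units.** With k batches there are 2k randomised groups and 2^k possible allocations. At k = 5 that is 10 groups and 32 allocations, with 40/10 = 4 to 120/10 = 12 centres per group. Groups equal centres only if each batch holds exactly two centres: 40/2 = 20 to 120/2 = 60 batches.

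**3. Smallest attainable p, MONOU alone.** A two-sided randomisation test that follows the described scheme cannot go below 2/2^k:

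| k | smallest p |
|---|---|
| 2 | 0.50 |
| 3 | 0.25 |
| 4 | 0.125 |
| 5 | 0.0625 |
| 6 | 0.031 |
| 10 | 0.002 |

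At least six batches are needed for p < 0.05 to be possible.

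**4. Type I error of a centre-level t test that ignores batch, MONOU alone.** Take 80 centres, k = 4, 10 centres per half, residual centre SD 1, and an assumed effect of SD s shared by all centres in a half.

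- True variance of an arm mean: 1/40 + s²/4.
- Variance the t test expects: [1 + (40/39)(s² − s²/4)]/40.
- s = 0.2: 0.0350 against 0.0258. The standard error is too small by a factor of 1.17, and rejection of a true null is about 9%.
- s = 0.3: 0.0475 against 0.0267. The factor is 1.33, and rejection is about 14% (13% to 14% in simulation).
- s = 0: 5%.
- At k = 8 with 5 centres per half, the same steps give about 7% and 9%.

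**5. The same test on the combined data.** Add 40 TROU centres, allocated singly, so that 40 of the 60 centres per arm carry a half-effect.

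- True variance: 1/60 + (40/60)² × s²/4. This is 0.0211 at s = 0.2 and 0.0267 at s = 0.3.
- Variance the t test expects: 0.0170 and 0.0175.
- Rejection: about 8% and 11% at k = 4; about 6% and 8% at k = 8.
- If the halves are also matched on a factor explaining 20% of variance (an assumption), simulation gives about 6% and 9% at k = 4, and 5% and 7% at k = 8.
- For MONOU alone with matching and no shared effect, rejection at k = 4 is about 3%, which is conservative.

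**6. The floor in the combined analysis.** If 40 TROU centres were split 20:20, TROU alone would have C(40,20), about 1.4 × 10¹¹, possible allocations. The floor in step 3 therefore does not carry over.

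**The case against.** The strongest reply is that this is a matter of wording. Elsewhere in the article cluster goes with the place of work. If the matched pair means two matched centres, units equal centres and most of the point goes. The statement that randomisation is identical to TROU's may refer only to the service and the ratio. The article also condenses a fuller protocol that may give the procedure. This reply cannot be excluded. But the text says that the accrued centres are divided into two clusters, and that this pair is randomised, which fits single pairs of centres poorly. The article states the unit in two ways, so the need to reconcile stands on any reading.

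Several stronger readings are tempting, and the documents do not support them:

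- *The split is made by hand by people who know the centres.* The sentence is passive and names no person or rule.
- *There are certainly far fewer units than centres.* That depends on k, which is not given.
- *The scheme biases the result or lets someone steer centres to an arm.* The division comes before the remote allocation, and each centre keeps a probability of 1/2 for either arm. Unlisted differences add variance, not bias.
- *The p-value floor undermines the main result.* The planned analysis combines MONOU with TROU, where centres are allocated by place of work.
- *The type I error is inflated.* This needs variance shared within halves. Nothing in the text says the division would sort centres on setting, region or management support, and successful matching works the other way.
- *The stated power is wrong for this reason.* The 200 is a count of staff and does not treat the centres as independently randomised. Whether batch enters the model may be settled in an analysis plan that is not shown.

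**Conclusion.** The point holds in limited form. The protocol describes two different randomised units for MONOU, and on the literal reading there is one random allocation per batch. That conclusion rests on the text alone.

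The consequences depend on what is not stated. For MONOU by itself, fewer than six batches would leave a randomisation test unable to reach p < 0.05. An assumed half-effect of 0.2 to 0.3 SD would take a batch-blind centre-level test to about 9% to 14% at k = 4. In the combined analysis the effect is partial: no floor, and about 6% to 11% at k = 4 under the same half-effects, depending on how well matching works. With no shared variance, the error rate is 5% or below. The treatment estimate is unbiased throughout. The change is worth making because it removes the dependence on these unknowns at very little cost.

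**What to change.** Reconcile the MONOU design section with both parts of its Randomisation section, and state one unit of randomisation.

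For centres still to be allocated, have the trials unit allocate each MONOU centre as its own unit, 1:1, by stratified blocks or by minimisation with a random element, on centre size and prior training (manual only, or manual and training). This keeps the balance the protocol wants and makes the centre the randomised unit.

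For batches already allocated, report how many there were and how each was divided. Include batch as a stratum in the analysis, and confirm the result with a re-randomisation test that re-draws MONOU allocation by batch and TROU allocation by centre.

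If pairs of single centres were meant all along, a corrected sentence saying so resolves the conflict.

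The cost is a changed request to the trials unit, slightly looser balance within a batch, and a little more analysis work. No extra centres or staff are needed.
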